#### Instruments and measures

##### Demographic and other personal data

Participants’ demographic information will be collected, including gender, age, previous residence, marital status, education, economic status, employment status, and duration of illness.

#### Primary outcomes

##### Patient adherence

The Medication Adherence Rating Scale (MARS) (Thompson et al., 2000) will be used in our study. The 10-item measure assesses patients’ attitudes, beliefs, and behavior toward taking medicine on a scale set to “yes” and “no” options for each item. The MARS is a reliable tool to measure medication compliance of patients with schizophrenia 1 week before the measurement point (Friemann and Wciórka, 2013).

#### Secondary outcomes

##### Self-compassion

Self-compassion will be measured using the Self-Compassion Scale (SCS) (Neff, 2003). This self-reported scale consists of 26 items designed to measure the six subcomponents of self-compassion: mindfulness, over-identification, sense of common humanity, isolation, self-kindness, and self-judgment; each item is rated on a 5-point scale. Item scores are used to generate a total self-compassion score. In the present study, the Chinese version of the SCS has shown good values for reliability and validity, and Cronbach’s α is set at 0.84 for the total score (Chen et al., 2011).

##### Stigma

Stigma will be measured using the Stigma Assessment Scale for mental illness, particularly in Chinese, a widely used measure of stigma (Zeng et al., 2009). This self-reported scale measures stigma along three dimensions: (1) socialization (related to the discrimination of patients in social and interpersonal communication), (2) competence (involves patients experiencing public discrimination against their personal abilities), and (3) therapy (related to patients’ experience of treatment, side effects, and neglect by medical staff). The scale is a self-reported measure comprising 32 items, and each item is rated on a 4-point scale. Item scores are used to generate a total stigma score. The scale has demonstrated good internal consistency in mental illness samples, and Cronbach’s α is set at 0.9.

##### Social support

Social support will be measured using the Social Support Rating Scale (SSRS) (Xiao and Yang, 1987). This self-reported scale consists of 10 items designed to measure the three dimensions of an individual’s social support: objective support (the actual support received by the patient), subjective support (the support that the patient can experience or emotional support), and support utilization (the active use of various social supports by individuals, including the way of talking, the way of asking for help, and the way of participating in activities). Item scores are used to generate a total social support score, and the higher the total score, the better the degree of social support. SSRS has good reliability and validity with Cronbach α and KMO of 0.72 and 0.637, respectively.

##### Program feasibility

Program enrollment, recruitment, retention, and diary completion data will be gathered to measure program feasibility: (1) enrollment rate = number of patients who meet inclusion criteria/number of people with schizophrenia; (2) recruitment rate = number of patients who agreed to participate in the study/number of patients who meet the inclusion criteria; (3) retention rate = number of patients who complete the intervention/number of patients who agreed to participate in the study; and (4) diary completion rate = actual number of completed journals/required number of completed journals.

##### Program acceptability

Participants’ satisfaction with and acceptability of the intervention will be assessed immediately after the intervention using eight single items on the Intervention Satisfaction Scale, which refers to the Intervention Satisfaction Scale by Campo et al. (2017). The content includes the acceptability of the intervention (two items) and the satisfaction of the intervention plan and implementation (six items), such as the frequency, duration, and length of the training. Our primary benchmark for acceptability is an average score of 4 or higher on participants’ responses to two items on this scale: (1) “Overall, I really enjoyed the self-compassion training” and (2) “I would recommend the self-compassion training to other patients with schizophrenia.” The other six items assessing satisfaction with the intervention are set to “yes” and “no” options for each item: “Generally speaking, I prefer online training,” “For me, a total of 3 weeks of training is appropriate,” “For me, about 45 min a day for training is the right length,” “For me, once a day of every task for 3 weeks is the right frequency,” “I am satisfied with the content of the training,” and “For me, most of the time I can complete my training in a quiet and undisturbed environment.”

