#### Secondary aim

To evaluate the effects of the WeChat-based self-compassion training program on self-compassion, stigma, and social support; evaluate the feasibility of online training by examining enrollment, recruitment, retention, and journal task completion rates; and determine satisfaction and acceptability of the program by assessing eight single items on the intervention satisfaction scale.

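### Three yes/no satisfaction items on amount (3 weeks, daily time, once a day) can show how many patients find it right, but not whether the others found it too much or too little

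*Protocol article*

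**What the plan says.** The Secondary aim includes to "determine satisfaction and acceptability of the program by assessing eight single items". The section Program acceptability divides the eight items into two on acceptability and six on satisfaction with the plan and its delivery. The two acceptability items (enjoyment, and recommending the training to other patients) carry the benchmark, a mean of at least 4.

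For the rest, the article fixes the response format: "The other six items assessing satisfaction with the intervention are set to" yes or no answers. Three of the six concern amount:

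- length: "For me, a total of 3 weeks of training is appropriate"
- daily time: "For me, about 45 min a day for training is the right length"
- frequency: "For me, once a day of every task for 3 weeks is the right frequency"

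The article describes no answer option for direction and no follow-up question. The form is given once, at T1. Statistical methods says that feasibility and acceptability will be summarised descriptively. No threshold or decision rule is attached to the six yes/no items.

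**The concern.** Whether an amount is right has three natural answers: too little, about right, too much. A yes/no format keeps the middle answer and pools the two outer ones. The same percentage of 'no' therefore fits a programme that patients found too heavy and one that they found too short. The information is lost when the form is filled in, so no later analysis can restore it.

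What is at stake is modest but relevant to this trial. Trial design calls the study exploratory, satisfaction is part of a named secondary aim, and the Conclusion foresees use in hospitals and communities if the programme is effective. Amount is also an open question on the article's own account: the Background lists online self-compassion programmes ranging from 6 weeks down to 1 week or less. A team preparing wider use would want to know which way dissatisfied patients lean.

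**Working it through.** **1. Number of respondents.** The only computed design figure is the sample size, which is needed here just for a plausible count. With effect size 0.3, power 0.80 and alpha 0.05 (taken as two-sided), the two-sample t-test calculation gives 175.4, rounded up to 176 per group. Allowing for 10% attrition, 176 / 0.90 = 195.6, rounded up to 196 per group and 392 in total. The stated figures reproduce. I take 176 to 196 respondents in the training arm as an assumption.

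**2. What the planned items can deliver.** For a 'yes' share p among n respondents, the 95% half-width is 1.96 × √(p(1 − p)/n).

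| 'Yes' share | n = 176 | n = 196 |
|---|---|---|
| 60% | ±7.2 points | ±6.9 points |
| 80% | ±5.9 points | ±5.6 points |
| 90% | ±4.4 points | ±4.2 points |

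The share who find the amount right is thus estimated to about ±4 to ±7 points.

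**3. What they cannot deliver.** Let q be the share answering 'no', made up of a (too much) and b (too little), with a + b = q. The net balance is a − b. The yes/no item fixes only q, so a − b can lie anywhere from −q to +q:

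- q = 20% (0.20 × 176 ≈ 35 patients): from −20 to +20 points
- q = 30%: from −30 to +30 points

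This range does not shrink with more patients.

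**4. The same quantity with three options.** Suppose that 80% of the dissatisfied lean one way and 20% the other. Then a − b = 0.6q in absolute value, and the 95% half-width is 1.96 × √((q − (0.6q)²)/n). With n = 176:

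- q = 0.20: 1.96 × √((0.20 − 0.0144)/176) = 0.064, about ±6 points
- q = 0.30: 1.96 × √((0.30 − 0.0324)/176) = 0.076, about ±8 points

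The 20% and 30% 'no' rates and the 80/20 split are illustrative assumptions, with no source in the article. The ambiguity itself needs none of them: it is present whenever anyone answers 'no'.

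**5. Whether other planned data supply the direction.** Retention and journal completion (Program feasibility) and the daily completion click (Self-compassion journal task) record whether tasks were done or reported as done. The weekly adverse event questions cover discomfort and distress. Each may hint at a heavy programme, but none asks whether patients wanted more or less. The Limitations section adds that use of the WeChat accounts cannot be monitored.

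**The case against.** The strongest reply is that nothing here is an error. The plan promises a descriptive account of satisfaction, and the 'yes' share gives one. It never undertakes to estimate a balance between too much and too little, and no decision hangs on these items. The Conclusion ties wider use to effectiveness, not to answers on length or frequency. The items are modelled on a published scale that is not at hand, and a condensed article need not show the whole form, so a comment field may exist. Retention, completion and weekly discomfort questions give some indirect sign of burden.

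Most of this stands, and it sets the size of the point. It does not remove it: the answer format is stated outright, and the direction is lost once the form is filled in.

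Three stronger readings are tempting and are not supported:

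- *That the result on amount is useless.* It is not. The 'yes' share has a clear meaning and adequate precision (step 2).
- *That the acceptability result is compromised.* The benchmark rests on two other, scored items. The three items on amount belong to the satisfaction set.
- *That the agreeable wording inflates a score.* The article describes no score formed from the six yes/no items, and gives nothing from which to size such an effect.

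**Conclusion.** The point holds in a limited form. The three items can show what share of patients find the length, daily time and frequency right. They cannot show in which direction the others were dissatisfied, and the article describes no other measure that can. With an illustrative 20% answering 'no', the unresolved range for the balance is 40 points wide (−20 to +20), against about ±6 points with three options. With 30%, it is 60 points wide, against about ±8. These figures rest on an assumed 176 respondents and, for the half-widths, on an assumed 80/20 split.

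The consequence is confined to a secondary, descriptive result. This is a cheap improvement of minor importance, not a flaw in the trial's main inference.

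**What to change.** On the online T1 form, replace yes/no for these three items by *too little / about right / too much*, adapting the words to each item (for example *too short / about right / too long* for the 3 weeks). Report the share answering *about right*, which takes the place of the planned 'yes' share, together with the share in each direction and 95% confidence intervals. Leave the other three yes/no items and the two benchmark items as they are.

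The cost is an edit to three items on one form, with no added item, visit or participant. The downsides are that these three items are no longer scored yes/no, and that comparability with the scale they were adapted from may be slightly reduced.

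A separate matter can be settled in the same edit. The daily-time item refers to about 45 minutes, while the times stated under the reading, meditation and journal tasks add up to 10 + 10 + 15 = 35 minutes. The two short reading tests have no stated time and may explain part of the gap. These sections need to be reconciled so that the item asks about the time patients actually spend. The point above does not depend on this.

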**Methods:**

The protocol for the randomized controlled trial (RCT) is based on the SPIRIT 2013 statement. This parallel RCT will aim to recruit 392 patients with schizophrenia who will be randomized at a 1:1 ratio into a 3-week intervention or control group. Both groups will receive routine care. The intervention group will also receive WeChat-based self-compassion training, which requires participants to complete three tasks every day, including a reading task, a meditation task, and a self-compassion journal task. The control group will receive WeChat-based psychological health education, which will only require participants to read positive articles about psychological health every day. Medication adherence, self-compassion, stigma, and social support will be measured at baseline (T_0_), immediately after the intervention (T_1_), and 3 weeks after the intervention (T_2_). Program feasibility will be evaluated throughout the course of the study, and acceptability will be measured immediately after the intervention (T_1_).

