##### Reading task

The content provided for reading will be updated daily according to the theme of the week. Participants will be able to read the new messages and review the message history of all content published on the WeChat public account. The messages will be shown in the form of text, videos, and pictures. The content of the first week will be focused on theoretical knowledge in relation to self-compassion. The aim is for participants to understand the meaning of the three levels of self-compassion and be able to start the self-compassion journal task. The second and third weeks will be focused on positive stories about people suffering from schizophrenia. These 2 weeks are a complement to the “sense of common humanity” gained in group therapy, where patients are able to view their experiences as part of a common experience of many people with schizophrenia (Lawrence and Lee, 2014), fostering acceptance by other group members (Ashfield et al., 2020). Reading new messages on the WeChat group will take approximately 10 min every day. At the end of the reading, two small tests will be inserted to check whether the participant has read the content carefully.

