##### Meditation task

In the 3-week online self-compassion meditation intervention, participants will be asked to listen to an audio recording regularly each week (at least once per day) (Albertson et al., 2015). Three different guided self-compassion meditations that were taught in the MSC program will be used for the intervention (Neff and Germer, 2013). For example, the first week will be the “compassionate body scan,” which aims to help the participant feel connected with their body and give their body sympathy, peace, and gratitude. Accompanied by the audio, the participants will be asked to sit or lie down, put their hands on their heart, remind themselves to be kind to themselves, and then scan from the top of their head to their feet and pay attention to the feeling of every part of the body. The task will take approximately 10 min every day.

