##### Self-compassion journal task

This task is a modification of the self-compassion journal exercise on [name] self-compassion website.^1^ The content of the weekly journal will differ in relation to the theme of the week. For example, in the first week, participants will be asked to “keep a journal from the perspective of mindfulness, a sense of common humanity and kindness.” They will be presented with prompts, such as “at some point during the day when you have a few quiet moments, write in your journal about anything that you felt bad about, anything you judged yourself for, or any difficult experience that caused you pain. For each event, use mindfulness, a sense of common humanity, and kindness to process the event in a more self-compassionate way.” Participants will be asked to try to write in their daily self-compassion journal for approximately 15 min, with guidance. All diaries will be delivered to the clinical psychiatric nurses via online documentation links on the WeChat public account, and participants will be instructed on the basis of their writing in order to better use the three components of self-compassion to help them actively cope with difficult emotions.

Task completion will be tracked every day. When the participant completes the task for the day, they will be required to click “I have completed the task” in the WeChat group; if the participant fails to complete the task before 8.00 p.m. that day, they will receive a private WeChat reminder message from the clinical psychiatric nurse. If participants have any questions about task completion, they will be able to leave a message on the WeChat public account, and the clinical psychiatric nurse will reply as soon as possible. All questions and answers on the WeChat public account will be visible to all participants in the intervention group (all the participants will be assured of anonymity by using special code numbers to identify themselves). The information forwarding function will be disabled, and participants will be told not to share the messages with others, such as by taking screenshots, in order to minimize potential contamination.

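### The stated times of the three daily tasks add up to about 35 minutes, but the one satisfaction item on daily length asks about 45, and the protocol does not explain the difference

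*Protocol article*

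**What the plan says.** The Methods paragraph of the abstract states that the intervention "requires participants to complete three tasks every day, including a reading task, a meditation task, and a self-compassion journal task". The Intervention section then gives each task a time:

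- Reading task: "Reading new messages on the WeChat group will take approximately 10 min every day". It adds, with no time given, "At the end of the reading, two small tests will be inserted to check whether the participant has read the content carefully".
- Meditation task: "The task will take approximately 10 min every day". On frequency it says "participants will be asked to listen to an audio recording regularly each week (at least once per day").
- Self-compassion journal task: "Participants will be asked to try to write in their daily self-compassion journal for approximately 15 min, with guidance".

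The section states no daily total.

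Under Program acceptability, satisfaction is measured immediately after the intervention with eight items. Two of them form the primary acceptability benchmark, a mean score of 4 or higher. The other six are yes/no items. One of these six concerns daily length: "For me, about 45 min a day for training is the right length". Another asks whether doing each task one time daily is the right frequency.

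**The concern.** The length item has a number of minutes built into it, and that number differs from the sum of the task times given a few pages earlier. A yes/no item of this kind can be interpreted only if its figure matches what the respondent was asked to do.

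If the training takes about 35 minutes, a participant who found that right may answer no because 45 would be too long, and a yes endorses a length that the participant did not experience. If it takes about 45 minutes, the item is sound but the task descriptions understate the load. Either way, a reader of the results would not know which daily length had been judged acceptable, and anyone repeating the programme would find two different daily loads in one protocol.

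The answers could not be adjusted afterwards from the data described. The Limitations section says that use of the public accounts cannot be monitored, and the journal section describes completion as a daily click, with no record of minutes.

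**Working it through.** **Inputs, all from the protocol article**

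- Reading: about 10 min per day (Reading task)
- Meditation: about 10 min per day (Meditation task)
- Journal: about 15 min per day (Self-compassion journal task)
- Length put to participants: about 45 min per day (Program acceptability)

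**Step 1. Sum of the stated times.** 10 + 10 + 15 = 35 min per day. The item's figure of 45 is not reproduced.

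**Step 2. Size of the gap.** 45 − 35 = 10 min per day. Relative to the sum, 10 / 35 = 29%. Relative to the item, 10 / 45 = 22%. The gap is as long as the whole stated reading task or the whole stated meditation task.

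**Step 3. Readings that would give 45.**

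| Reading | Arithmetic | Support in the text |
|---|---|---|
| Meditation twice a day | 10 + 20 + 15 = 45 | Allowed, because the stated frequency is a minimum. Against it, the meditation section gives the daily task as about 10 min, and the frequency item in the same questionnaire describes each task as done one time daily. |
| Fifteen minutes for every task | 3 × 15 = 45 | Contradicts the times given for reading and meditation. |
| Reading tests take the remainder | 35 + 10 = 45 | No time is stated. The tests would have to last as long as the reading, yet they are called small. |
| Journal submission and feedback take the remainder | 35 + 10 = 45 | No time is stated for either. |

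A mixture of the untimed activities could also fill part of the gap. The protocol states none of these explanations.

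**The case against.** The strongest reply is that 35 minutes is not the protocol's own total. It is a sum of three approximate figures, each attached to a core activity: reading the messages, the meditation task, writing the journal. Participants also take two tests, submit the journal, receive guidance on it and confirm completion, and they may listen to the recording more than once. A rounded figure of about 45 for the whole daily effort could cover some of this. That part stands: the text does not rule it out, and real time may exceed 35 minutes for some participants.

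It follows that a reader should not infer from the sum that 45 is the mistake, or that the item asks about a programme that will not be delivered. The documents establish neither the minutes actually delivered nor which figure is in error.

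It is also fair to say that the stakes are low. This is one of six yes/no satisfaction items on a secondary outcome, and the Statistical methods section plans only descriptive statistics for acceptability. The benchmark rests on two other items. Multiplying the gap over 21 days (21 × 10 = 210 min, or 3.5 hours) adds no weight, since no analysis uses cumulative time.

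What the reply does not do is explain the difference. Approximate wording alone is a weak account of a 29% gap, and the possible explanations have to be supplied by the reader.

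**Conclusion.** The inconsistency is real but minor. The stated task times sum to about 35 minutes a day, the questionnaire item says about 45, and the protocol does not account for the 10-minute difference. As long as this stands, the answers to the single item on daily length will be hard to interpret, and the published training load will be ambiguous.

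The effect stops there. The adherence outcome, the efficacy analysis, the sample size, the primary acceptability benchmark and the other satisfaction items are untouched.

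The conclusion assumes that the three timed tasks are the only timed daily components, which is how the article presents them, and that the item will be used with the wording printed. It does not depend on which of the two durations is right.

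**What to change.** Either of two changes is enough:

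1. Reconcile the three task descriptions with the satisfaction item, without presuming which duration is right. If untimed activities or repeated meditation are meant to be part of the daily length, the text should say so and give the total once.
2. Reword the item so that it carries no figure, for example: *the daily length of the training was right for me*. The answer then refers to whatever the participant actually experienced.

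The second change makes the item interpretable but leaves the described load as it is, so a short clarification of the total would still help anyone repeating the programme.

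The cost is one questionnaire line, or a sentence or two of protocol text. The Conclusion describes the trial as still to be implemented, so the change can be made before the T1 questionnaire is issued. Once T1 answers are collected, the item cannot be repaired from the data described.
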